## Abstract

**Background:**

HIV incidence among South African adolescent girls and young women (AGYW) remains high, but could be reduced by highly effective pre-exposure prophylaxis (PrEP). Unfortunately, AGYW report significant barriers to clinic-based sexual and reproductive health services. Even when AGYW access PrEP as an HIV prevention method, poor prevention-effective use was a serious barrier to achieving its optimal HIV prevention benefits. Determining the acceptability and feasibility of community-based platforms to increase AGYW’s access to PrEP, and evaluating behavioural interventions to improve prevention-effective use of PrEP are needed.

**Methods:**

We propose a mixed-methods study among AGYW aged 16–25 years in Eastern Cape Province, South Africa. In the first component, a cross-sectional study will assess the acceptability and feasibility of leveraging community-based HIV counselling and testing (CBCT) platforms to refer HIV-negative, at-risk AGYW to non-clinic-based, same-day PrEP initiation services. In the second component, we will enrol 480 AGYW initiating PrEP via our CBCT platforms into a three-armed (1:1:1) randomized control trial (RCT) that will evaluate the effectiveness of adherence support interventions to improve the prevention-effective use of PrEP. Adherence will be measured over 24 months via tenofovir-diphosphate blood concentration levels. Qualitative investigations will explore participant, staff, and community experiences associated with community-based PrEP services, adherence support activities, study implementation, and community awareness. Costs and scalability of service platforms and interventions will be evaluated.

**Discussion:**

This will be the first study to assess the acceptability and feasibility of leveraging CBCT platforms to identify and refer at-risk AGYW to community-based, same-day PrEP initiation services. It will also provide quantitative and qualitative results to inform adherence support activities and services that promote the prevention-effective use of PrEP among AGYW. By applying principles of implementation science, behavioural science, and health economics research, we aim to inform strategies to improve access to and prevention-effective use of PrEP by AGYW.

**Trial registration:**

ClinicalTrials.govNCT03977181. Registered on 6 June 2019—retrospectively registered.

## Background

In 2017, 1.8 million people were infected with human immunodeficiency virus (HIV), most of whom live in Southern and Eastern Africa [1]. There exist significant differences in HIV incidence and prevalence by age and sex, with young women being particularly vulnerable to HIV [2–7]. In South Africa, specifically, HIV incidence and prevalence among adolescent girls and young women (AGYW) ages 15–24 is significantly higher than their male counterparts (incidence = 1.51% per year vs. 0.49% per year, respectively; prevalence = 10.9% vs 4.8%, respectively) [8]. Significant risk factors include having concurrent or older sexual partners [9–11] as well as interpersonal violence [12, 13]. Consequently, there is an urgent need for effective HIV prevention strategies targeted at young women and under their control, to reduce HIV incidence among this key population.

Pre-exposure prophylaxis (PrEP) with emtricitabine (FTC)/tenofovir (TDF) as a method of HIV prevention has demonstrated significant efficacy in clinical trials among different population groups, with efficacy being strongly associated with increased drug adherence [14–18]. Previous and current PrEP demonstration projects have largely focused on providing PrEP through clinic-based delivery platforms, including antiretroviral therapy (ART), sexually transmitted infections (STI), family planning, and adolescent-friendly clinics [19–21]. While clinic-based services may provide good opportunity for service integration, leveraging these facility-based services for PrEP provision may be fraught with barriers including perceived lack of confidentiality and privacy at health centres [22–24], unfriendly clinic staff [25, 26], long queues, inconvenient operating hours, and a perceived predominant focus on maternal-child health with no AGYW-focused services [27, 28].

Interventions associated with adolescent health should be adolescent-centred, with services leveraging community-based delivery platforms and not rigid, medicalized, clinic-based venues [29]. Recent findings from an at-scale community-based HIV counselling and testing (CBCT) programme implemented in South Africa found that AGYW had the highest testing uptake across all age groups of either sex, regardless of district type (i.e. urban, rural, peri-urban) [30]. Given that HIV testing is the entry point for PrEP service delivery, leveraging CBCT platforms to effectively identify and link young women to PrEP services should be considered as a supply-side intervention for scaling up PrEP.

Community-based programmes aimed at supporting ART adherence and retention in care have been recognized as effective and sustainable approaches to achieving the UNAIDS 90-90-90 targets [31–37]. One of the most innovative and successful adherence support interventions has been “adherence clubs”. Adherence clubs are a cost-effective intervention strategy that can be locally adapted to low-resource settings and implemented by non-specialists and lay health workers with little formal counselling experience [37–40]. As PrEP becomes more widely available, rigorously evaluated adherence skill-building interventions, implemented through community-based platforms, will provide invaluable information regarding the optimal structure, content, and delivery of PrEP adherence support programmes.

## Study rationale and aims

Few studies have explored effective strategies to identify and deliver non-clinic-based PrEP services to at-risk populations, how to support prevention-effective use and retention in PrEP care, or implementation science approaches to scaling up PrEP delivery. Given that CBCT platforms have been shown to be highly acceptable and accessible to adolescent girls and young women, it is crucial to understand if these platforms can also be used to identify and deliver PrEP to at-risk youth [14–16]. Furthermore, community-based prevention-effective PrEP adherence support is critical to reduce the HIV burden among AGYW in South Africa. Towards this, our study aims include (Table 1):
Aim 1: PrEP service delivery: To determine the acceptability and feasibility of PrEP uptake by AGYW when delivered through community-based HIV counselling and testing platforms;Aim 2: PrEP adherence support: To evaluate community-based, scalable interventions to achieve prevention-effective adherence to PrEP among AGYW; andAim 3: Scalability of community-based PrEP services: estimate the cost per AGYW initiated on PrEP and provided adherence support through community-based platforms, and the cost per incident HIV infection averted.

**Table 1 Tab1:** Study overview: aims, rational, hypothesis, design and outcomes

	Hypothesis	Rational	Study design and approach	Primary outcome	Secondary outcomes
**Aim 1**	CBCT platforms will facilitate access to and initiation of PrEP by adolescent girls and young women	Numerous barriers exist that delay or inhibit YW’s access to clinic-based reproductive health and HIV prevention services	Cross-sectional, mixed methods. Integrate PrEP initiation services into CBCT pop-up testing sites and home-based testing platforms in extremely high HIV burden and under-researched rural and urban settings of South Africa	The proportion of eligible young women accepting PrEP as part of CBCT services	(1) PrEP initiation rates by a) community type (urban vs. rural), and b) CBCT platform (*pop-up testing sites vs systematic home-based testing*); (2) In-depth qualitative understanding of immediate, delayed and never accepting PrEP; (3) Socio-demographic and behavioural correlates of immediate, delayed and never initiating PrEP
**Aim 2**	Cognitive behavioural-based adherence support programmes will be associated with a substantial increase in prevention-effective use of PrEP compared to a control	Lack of PrEP efficacy in African YW in clinical trials was strongly associated with poor adherence. To maximize the prevention benefits of PrEP, scalable adherence support interventions are needed	Randomized controlled trial. Enrol and randomize *PrEP-accepting young women* to receive one of two adherence support interventions or standard care (basic adherence support)	Comparison of tenofovir-diphosphate concentration levels in dried blood spots by study arm, with a 12-month primary outcome and 24-month assessment of intervention durability	(1) Predictors of PrEP adherence after adjusting for study arm, socio-demographic factors, exposure to adherence support activities, and risk profiles; (2) Characterization of changes in sexual behaviours and risk profiles following PrEP initiation; (3) Proportion of individuals that discontinue PrEP and factors associated with discontinuation; and (4) Qualitative description and factors associated with of patterns of PrEP use
**Aim 3**	Community-based PrEP initiation and adherence support platforms will increase uptake of and adherence to PrEP among YW, and cost-effectively avert HIV infections compared to standard practice	Evidence on cost and cost-effectiveness can be used by decision makers regarding the use of resources to support PrEP scale-up	Mathematical modelling and micro-costing studies. Estimate incremental costs and cost-effectiveness of community-based PrEP initiation and adherence support programmes among YW relative to standard practice.	Estimate the cost-effectiveness and budget impact of targeted PrEP initiation and adherence support	(1) Micro-costing studies will evaluate costs incurred and costs averted; (2) Estimate impact of support interventions on HIV incidence, HIV-related deaths and DALYs, using proportion on PrEP

## Methods

### Study design and flow

The Community PrEP Study will enrol a cohort of 480 HIV-negative South African AGYW aged 16–25 years, incorporating multiple study designs to address our three main study aims (Table 1). Specifically, a cross-sectional, mixed-methods study design will be used to quantitatively measure and qualitatively assess the acceptability and feasibility of using CBCT platforms to identify HIV-uninfected AGYW and offer PrEP (Aim 1). A randomized controlled trial will evaluate a behavioural intervention aimed at supporting prevention-effective adherence to PrEP (Aim 2). Finally, we will perform micro-costing and mathematical modelling analyses to calculate the cost-effectiveness of our PrEP delivery platform and adherence support programmes (Aim 3). Community advisory boards (CABs) were established to facilitate community engagement and acceptance, elicit feedback on study design, conduct analysis, and ensure that community views and perspectives were appropriately incorporated in a collaborative manner.

### Study location

This study is being conducted in Buffalo City Metro (BCM) Health District, Eastern Cape Province, South Africa (Fig. 1). In 2016, BCM had an estimated mid-year population of 834,998 people. In 2016, the South African National Department of Health estimated that BCM had a general population HIV prevalence of 12.4% and incidence of 0.54%; an adult (15+ years old) HIV prevalence of 17.1% and incidence of 0.74%; and a female youth (age 15–24 years) HIV prevalence of 12.8% and incidence of 2.40% [41]. Within BCM, our study will be conducted in one urban and one rural community. Selection of study communities was conducted in consultation with the BCM Department of health and was informed by census data, absence of other ongoing HIV prevention studies, and community willingness to be involved in the study.

**Fig. 1 Fig1:**
[figure not shown]
Provincial map of South Africa showing location of study communities within Buffalo City Metro Health District, Eastern Cape Province

### Intervention design and adherence support activities

#### Description of the intervention

The intervention arms were developed using the Information-Motivation-Behavioural Skills Model of Behaviour Change (IMB) [42, 43]; the IMB model has been used extensively to improve medication adherence, including for ART [42–44] and daily contraceptives [45]. Intervention arms will incorporate content from the evidence-based intervention Life Steps [46], as well as from the HIV Prevention Trials Network 082 study [47] and the 3Ps for Prevention open-label PrEP demonstration study [48]. Using standardized manuals, adherence support interventions will be delivered in either a group (Arm 1) or one-on-one individual (Arm 2) sessions. Participants randomized to intervention arms will be seen by adherence counsellors monthly for 24 months at a fixed community-based site.

#### Control

Control participants will receive passive adherence support consistent with standard of care for PrEP programmes delivered by public sector health clinics. Control participants will return monthly to collect medication refills, report and receive support for side effects, and conduct special study activities (i.e. specimen collection; Table 2).

**Table 2 Tab2:** Study related events and time points

	Baseline	M1	M2	M3	M6	M9	M12	M15	M18	M21	M24
**Routine study activities**											
**HIV and pregnancy testing**	**X**			**X**	**X**	**X**	**X**	**X**	**X**	**X**	**X**
**Group and individual adherence support**		**X**	**X**	**X**	**X**	**X**	**X**	**X**	**X**	**X**	**X**
**PrEP medication pickup**	**X**	**X**	**X**	**X**	**X**	**X**	**X**	**X**	**X**	**X**	
**Special study activities***											
**ACASI Questionnaire**	**X**			**X**			**X**				**X**
**CrCl testing**	**X**			**X**			**X**				**X**
**STI testing**	**X**				**X**		**X**				**X**
**Blood testing for detectable TFV-DP**				**X**	**X**		**X**		**X**		**X**
**Hepatitis B testing and vaccination**	**X**	**X**			**X**						

* A R30.00 (~$2.00) voucher will be provided after each “special” study visit where specimens are collected (i.e. M3, 6, 12, 18, and 24)

Monthly activities will include (1) attendance check-in, (2) adherence support session (intervention arms only), (3) clinical assessment, (4) medication dispensing, (5) study visit reminders, and (6) study pack and voucher. Each month, study staff will contact participants up to three times via SMS and phone calls as study visit reminders to support retention. More details about intervention and control arms is available in Table 3.

**Table 3 Tab3:**
[figure not shown]
Components of adherence interventions

*Study packs included sanitary pads, condoms, snack, and medication refill reminder card

### Randomization

Randomization will occur following participant consent and confirmatory pregnancy testing. Independent random allocation lists will be created by the study Data Manager for each study site (urban vs. rural), with study staff and participants blinded to the allocation scheme. Participants will be randomized to study arms in a 1:1:1 ratio using computer-generated quasi-random numbers and permuted blocks of 18, within the randomization module of Research Electronic Data Capture (REDCap) [49]. Since the randomization occurs at the community-based study sites, it is impossible to blind study team members or participants to the randomization assignments. However, procedures to minimize the influence of the unblinded nature of this study on outcomes have been implemented. Ongoing data monitoring does not include information about study endpoints disaggregated by study site or study arm. Although the study biostatistician reviews data on PrEP uptake and adherence by study arm and site, the final outcome is always blinded.

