### Sample size and power calculations

A sample size was calculated to have 80% power to detect differences in the proportion of participants adhering to PrEP among the three study arms (Aim 2) using the chi-square test for independence with two degrees of freedom, with an alpha of 0.05, and assuming an attrition rate of 10% for those who (1) withdraw voluntarily from the study, (2) initiate on PrEP but withdraw due to adverse events (e.g. hepatic or renal abnormalities), or (3) become ineligible for PrEP (e.g. seroconvert). The effect size estimate was informed by prior experience from the field, where an effect size of 0.30 has been found between ART clients receiving some adherence support and those receiving none. However, we use a more conservative effect size of 0.15, to account for the fact that adherence support may not lead to the same gains in adherence among HIV-negative PrEP clients as it does with HIV-positive ART clients. The sample size was calculated to be 160 per arm (480 total).

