### Data analysis

Descriptive statistics (e.g. means, standard deviations/variances, medians with inter-quartile ranges, and frequency distributions) will be used to describe participant demographic characteristics. The chi-squared statistic test will be used for categorical variables whereas T-test (parametric) or Wilcoxon rank sum test (non-parametric) will be applied for continuous variables. Transformations of outcome variables will be explored and performed if appropriate. Multivariate logistic regression models will be performed to examine associations between covariates. Since data is collected on one subject over time, the data will be treated as longitudinal data. Generalized linear mixed effect models will be fitted to determine associations of interest with time and intervention effects included as fixed effects and allowing for subject-specific random effects. Alternatively, generalized estimating equations can be used to account for any correlations of repeated data measures, when assessing determinants of PrEP adherence at time points provided we have balanced data with ignorable missing patterns. Time-to-event analysis will be conducted using Kaplan-Meier plots. To determine possible associations with covariates, a Cox-proportional hazard will be used. If the proportional hazard assumption does not hold, an accelerated failure time model will be used. Missing data due to loss to follow-up is inadvertent and inevitable. The extent of missing data will be assessed in the primary analysis. The primary analysis will be conducted under the assumption of data Missing at Random (MAR). As such, longitudinal likelihood-based data analysis, utilizing all the observed pre-deviation data from each participant will be employed. Thereafter, multiple imputation (MI) method will be employed under the primary MAR assumption, and Rubin’s rule will be followed to combine results. Sensitivity to deviation from the MAR assumption will be investigated. Intention to treat (ITT) assessment with complete case approaches where necessary will be implemented in cases of non-adherence to randomization assignment. Depending on the extent of non-adherence, the “as treated (AT)” approaches may be employed to analyse participants according to the intervention received regardless to their randomized allocation. A marker of level of adherence can also be included in the models. Patterns of PrEP use will be identified using latent class models or clustering techniques and the association of factors with these latent classes will be examined using multinomial logistic regression modelling. For all statistical investigations, tests for significance will be two-tailed. Analyses will be conducted using STATA 13.0 or R version 4.

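### Randomisation is stratified by urban and rural site, but no Aim 2 quantitative analysis names site; adding it is a small, free gain, and neither validity nor the sample size is at stake

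*Protocol article*

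**What the plan says.** The Randomization section sets up stratified allocation: "Independent random allocation lists will be created by the study Data Manager for each study site (urban vs. rural"). It adds: "Participants will be randomized to study arms in a 1:1:1 ratio using computer-generated quasi-random numbers and permuted blocks of 18". Arms are therefore balanced within the urban site and within the rural site.

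The Sample size section sizes Aim 2 "using the chi-square test for independence with two degrees of freedom, with an alpha of 0.05". No stratification is mentioned.

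The Data analysis section describes generalised linear mixed models "with time and intervention effects included as fixed effects and allowing for subject-specific random effects", with generalised estimating equations as an alternative. It also names a chi-squared test for categorical variables, again without strata.

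Elsewhere, urban versus rural appears as a breakdown of Aim 1 PrEP initiation and as context in the qualitative work. The Aim 2 adjustment set for predictors of adherence (Primary and secondary outcomes) lists study arm, socio-demographic factors, exposure to support and risk profiles. Site is not in it.

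**The concern.** Blocked allocation within site removes most of the chance imbalance in site between arms, so site differences contribute little to the true sampling variance of the arm comparison. An analysis without site still counts the between-site variation as noise. If adherence differs between the two communities, the estimated variance is then larger than the true one. The test rejects less often than its nominal level, and power that the design has already paid for is not used.

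The article treats site differences as plausible. Table 4 plans a staff exchange to look for differences between sites that could affect adherence and attendance. What is at stake is efficiency and agreement between design and analysis. A false-positive finding is not the risk.

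**Working it through.** **Inputs from the article.** 1:1:1 allocation in blocks of 18 within two sites; 2-df chi-square; alpha 0.05; 80% power; effect size 0.15; 10% attrition; 160 per arm, 480 in total.

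**Assumptions (not in the article).** Effect size 0.15 is Cohen's w; the two sites are equal in size; overall high adherence p is 20–50%; the site gap g is 0, 10, 20 or 30 percentage points.

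**Step 1: reproduce the stated sample size.** For 80% power with 2 df at alpha 0.05, the noncentrality is 9.635.
- N = 9.635 / 0.15² = 9.635 / 0.0225 = 428.2, so 429 evaluable.
- 429 / 0.9 = 476.7, so 477, or 159 per arm. The stated figure is 160 per arm.
- With 480 × 0.9 = 432 evaluable, the noncentrality is L = 432 × 0.0225 = 9.72 and power is 80.4%.

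The stated figure is reproduced.

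**Step 2: share of outcome variance due to site.** For two equal sites, R = (g/2)² / [p(1 − p)].
- g = 0.20, p = 0.50: R = 0.01 / 0.25 = 4.0%.
- g = 0.20, p = 0.20: R = 0.01 / 0.16 = 6.3%.

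With a fraction f in one site the numerator is f(1 − f)g². This is largest at f = 1/2, so an unequal split gives a smaller share for the same g and p.

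**Step 3: standard error and type I error.** An analysis without site overstates the standard error by the factor 1/√(1 − R). The unstratified statistic behaves as (1 − R) times a chi-square. The 2-df tail area is exp(−x/2), so the type I error is 0.05^(1/(1 − R)). At g = 0.20 and p = 0.50 this is 0.05^(1/0.96) = 0.044.

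**Step 4: power.** The site-stratified test has noncentrality L/(1 − R). The unstratified test has the same noncentrality, but its critical value is in effect raised from 5.991 to 5.991/(1 − R).

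Ranges below are over p = 20–50%.

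| Site gap | R | SE too large by | Type I error, unstratified | Power, unstratified | Power, stratified |
|---|---|---|---|---|---|
| 0 | 0 | 0 | 5.0% | 80.4% | 80.4% |
| 10 points | 1.0–1.6% | 0.5–0.8% | 4.8–4.9% | 80.4–80.5% | 80.8–81.0% |
| 20 points | 4.0–6.3% | 2.1–3.3% | 4.1–4.4% | 80.6–80.8% | 82.1–83.0% |
| 30 points | 9.0–14.1% | 4.8–7.9% | 3.1–3.7% | 81.0–81.4% | 84.2–86.3% |

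**Step 5: simulation.** 20,000 runs per setting, 240 randomised per site, blocks of 18, 10% random loss, overall adherence 30%; Pearson chi-square against the site-stratified Cochran-Mantel-Haenszel test.

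| Site gap | Type I error, Pearson v stratified | Power, Pearson v stratified |
|---|---|---|
| 0 | 4.8% v 4.8% | 82.0% v 81.8% |
| 10 points | 4.7% v 4.8% | 82.4% v 82.8% |
| 20 points | 4.6% v 5.2% | 82.3% v 84.4% |
| 30 points | 3.7% v 5.1% | 83.1% v 87.0% |

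The simulation error of a type I estimate is about √(0.05 × 0.95 / 20,000) = 0.15 points. The simulation agrees with the formulas in direction and in rough size.

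**The case against.** A reader might infer that the plan excludes site. It does not. The Data analysis section describes a family of models and names two fixed effects, without saying that these are the only ones. The article is condensed, and a fuller covariate list may stand in a statistical analysis plan that is not shown. This objection limits the point but does not remove it: the article goes as far as listing model terms, and the one factor built into the Aim 2 allocation is not among them.

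A reader might also take the unstratified chi-square as the planned primary test. The article uses it as the basis for the sample size, and sizing on an unstratified test before an adjusted analysis is ordinary practice. The chi-squared test in the Data analysis section follows a sentence on describing participants and is not designated as the primary arm comparison. What that section attaches to the primary analysis is a longitudinal likelihood-based approach under data missing at random.

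A third tempting inference is that standard errors are wrong in a way that invalidates the comparison or leaves the trial underpowered. The error runs in the safe direction, and the unstratified test keeps at least its planned 80% power throughout the range examined.

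Two further limits stand. In a logistic mixed model, adding site need not shrink the standard error of the conditional odds ratio, so a claim of uniformly narrower intervals would be wrong there. And the staff exchange is a one-day qualitative exercise: it makes a site difference plausible but says nothing about its size.

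**Conclusion.** The point holds as a minor one. Site is the randomisation stratum and is not named in the Aim 2 quantitative analysis. If adherence differs by site, following the model terms as listed gives a valid but somewhat conservative comparison.

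The loss is nil with no site gap, at most about 2 points of power for gaps up to 20 points, and about 3–5 points only at a 30-point gap. These figures are for the 2-df test on high adherence and depend on the assumed gaps, equal sites, 20–50% overall adherence and 432 evaluable participants. The article does not show which gap applies. What is forgone is extra power above the target, and the total of 480 stands.

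**What to change.** - Name site (urban or rural) as a fixed effect in the month-12 primary model and in the longitudinal models.
- Report the site-standardised risk difference for high adherence, or the site-adjusted mean difference if the TFV-DP concentration is analysed as continuous.
- If a chi-square is used to compare high adherence between arms, use its site-stratified 2-df Cochran-Mantel-Haenszel form.
- If the analysis is a logistic mixed model, justify the site term by power and agreement with the design, and do not promise a smaller standard error for the conditional odds ratio.

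The cost is one binary covariate already known from the allocation lists, with no new data, participants or procedures. Enrolment is complete, but this is an analysis-only change and remains possible. It should be fixed and dated before arms are compared on outcomes. A record of the date matters because the Randomization section lets the study biostatistician review adherence by arm and site. If the full analysis plan already includes site, one sentence saying so settles the point.
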